### Outcome measures

An overview of outcome measures collected at each time point is provided in table 3.

#### Primary outcome measures

##### Forgotten Joint Score-12

Patients assess their knee joint awareness using the Forgotten Joint Score-12 (FJS-12), which consists of 12 items rated on a 5-point Likert scale in different daily living situations. The results are summarised into a total score on a 0–100 scale, with 0 indicating worst (high joint awareness) and 100 indicating best (low joint awareness).^15^ Lower awareness of the operated joint is considered to reflect higher postoperative satisfaction. Psychometric properties of the FJS-12, including minimal clinically important difference (MCID), minimal important change (MIC), minimal detectable change and patient-acceptable symptom state thresholds, have been previously determined using patient satisfaction with surgery (5-point Likert scale: very satisfied, satisfied, neither satisfied nor dissatisfied, dissatisfied, very dissatisfied) as an anchor.^16^ The FJS-12 demonstrates good validity and reliability, with low floor and ceiling effects and is well suited for a population of Swedish patients undergoing TKR.^39 40^

##### Modified Patient Enablement Instrument-2

The modified Patient Enablement Instrument-2 (Mod-PEI-2) is based on the PEI-2, a 6-item PROM in which patients assess their ability to cope with life, understand and manage their disease, maintain health and help themselves. In the original version, patients respond based on information received at a prior doctor’s appointment, whereas in this modified version, patients evaluate their coping abilities over the previous 4 weeks, regardless of any intervention received. Items are rated on a 5-point Likert scale, ranging from ‘extremely well’ to ‘not at all’. Scores are summed to give a total ranging from 6 to 30, with higher scores indicating greater enablement.^41^ Both the Mod-PEI-2 and the Swedish version of the original instrument have demonstrated good validity, reliability, sensitivity and responsiveness, making them suitable for use in intervention studies.^42 43^

### Secondary outcome measures

#### Patient satisfaction 52 weeks after surgery

52 weeks after surgery, patients are asked to respond to the question, ‘How satisfied are you with the results of your surgery?’ using a single-item, 5-category Likert scale with the following response options: very satisfied, satisfied, neither satisfied nor dissatisfied, dissatisfied or very dissatisfied. This single-item measure of satisfaction has been tested in a large-scale arthroplasty registry and is internationally recognised as a valid and relevant measure of patient satisfaction.^44 45^

#### Patient-reported function and health-related quality of life

Patient-reported function and health-related quality of life are assessed using the Knee injury and Osteoarthritis Outcome Score (KOOS) and the EuroQol 5 Dimensions 3 Levels (EQ-5D-3L) questionnaires. KOOS has demonstrated adequate measurement properties across different knee injuries and age groups, including older adults with knee OA undergoing TKR.^46 47^ The EQ-5D-3L shows good reliability and validity but is less responsive than the 5L version in patients undergoing TKR.^48^

#### Physical activity and sedentary habits

Physical activity is assessed using the short version of the International Physical Activity Questionnaire (IPAQ-SF). While patient-reported outcomes have limitations in measuring physical activity and sedentary behaviour—patients tend to under-report low-intensity activities and sedentary behaviour and over-report higher-intensity activities—the IPAQ-SF is considered an acceptable tool for patients with knee OA, where the collection of patient-reported outcomes is feasible.^49 50^

Objective physical activity is measured using the activPAL accelerometer. The device is attached with waterproof tape to the front of the affected thigh and worn 24 hours a day for 7 consecutive days. Using the activPAL accelerometer to collect objective measures of physical activity is a feasible method that provides acceptable accuracy for estimating activity levels in free-living individuals.^51 52^

#### Objective function

Isometric quadriceps strength is measured with the patient seated in 90° knee flexion using a fixed dynamometer (Meloq Easyforce, product no. 2009002), without back support, and with hands resting on the plinth. Following instructions, patients familiarise themselves with the test by performing two submaximal repetitions, followed by two maximal repetitions of three seconds each on both legs, starting with the non-affected leg. The highest value achieved (in Newtons) for each leg is recorded as the result. Isometric testing of quadriceps strength is suitable for patients undergoing TKR and may be associated with lower pain during testing compared with isotonic testing.^53^

Active knee range of motion is measured with the patient supine using a long-arm goniometer. The maximal active, unassisted extension and flexion angles are recorded for each leg, starting with the non-affected leg. This method of measuring active knee ROM is reliable and provides acceptable accuracy, although it tends to slightly underestimate knee flexion angles.^54 55^

Functional performance is assessed using the 30 seconds Chair to Stand-Test (30s CST), in which the patient completes as many sit-to-stand repetitions as possible in 30 seconds from a standard-height chair (45 cm) with arms crossed over the chest. The 30s CST is recommended by the Osteoarthritis Research Society International for patients with knee OA and demonstrates good reliability and validity.^56^,^58^

### Other measures

#### Adherence

Adherence to the intervention is recorded using an exercise journal maintained by the physiotherapist overseeing the intervention. Patients’ attendance and participation in each session are documented, along with the education topics discussed with each patient during every session. The journal tracks the number of exercises performed, variation of exercises, dosage and load used and the SANE score for each patient at every session. Educational topics discussed are recorded individually for all patients, although the detailed content of these discussions is not documented. Patients without a scheduled surgery date after the 8-week intervention who choose to continue exercise therapy, either supervised or unsupervised, maintain an identical exercise journal and record their own sessions. To support continued adherence, check-ins by phone or video conference with the physiotherapist in charge are scheduled every other week, as previously described.

For patients assigned to standard care, any participation in ongoing exercise interventions outside the trial is recorded using patient-reported forms at baseline and at the 8-week and 1-week pre-surgery follow-ups. This includes the type of exercise performed, its duration and weekly frequency. Participation in the standardised preoperative education session is also documented.

#### Description of surgical procedures and postoperative physiotherapy

Information about the surgical procedure, including type of replacement, use of patella button/resurfacing and any soft tissue procedures beyond standard practice, is collected from the surgery report. Anthropometric data, such as weight, height, body mass index and American Society of Anesthesiologists (ASA) physical status classification, are obtained from the preoperative anaesthesiologist assessment.

Physiotherapy care is not standardised after the initial 6-week postoperative programme; therefore, a brief description of postoperative physiotherapy management is collected at the 6-week, 12-week and 52-week postoperative follow-up assessments.

#### Adverse events

Adverse events, including injuries sustained during intervention participation, re-surgeries (with reasons), postoperative infections and deaths, are recorded for all patients.

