### Randomisation

Patients are randomised using opaque, concealed envelopes and stratified by age (≤67 years, >67 years) with a 1:1 allocation ratio, based on computer-generated random number sequences, into the intervention group, comprising prehabilitation in addition to standard care (SC+P), or the control group, consisting of standard care only (SC). The computer-generated random number envelope sequences were created by a person not otherwise involved in the trial. Allocation is performed by the trial coordinator immediately after the baseline assessment. The trial coordinator did not have access to the randomisation lists before allocation.

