### Prehabilitation

Prehabilitation consists of 8 weeks of on-site, supervised and individualised exercise therapy together with patient education. It is delivered in a group format two times per week, at a fixed time in the afternoon (approximately 1 hour per session), by physiotherapists with experience in the rehabilitation of OA and TKR.

After the 8-week intervention, patients are advised to continue the exercise therapy either in supervised sessions or unsupervised at a location of their choice until the surgery date. Patients who choose to continue with unsupervised exercise therapy have check-ins scheduled by phone or video conference every other week with the physiotherapist in charge of the intervention to discuss exercise progression and adjustments.

Physiotherapists at the participating clinics are trained in the intervention’s content and structure two times before enrolling patients. They work with the trial coordinator to review these materials, and monthly meetings are held to monitor sessions, ensure treatment fidelity and address any issues.

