### Standard care

Before surgery, standard care consists of self-care and a single, standardised 1.5-hour preoperative education session, delivered approximately 2–3 weeks before surgery. General oral and written information is provided regarding preparations for surgery (eg, preparing the home environment), events during the hospital stay and initial postoperative rehabilitation. No specific preoperative exercise advice is given. The standardised preoperative education session is delivered by healthcare staff (physiotherapist, occupational therapist, nurse) who are not involved in the present trial.

During the hospital stay (1–2 overnights) after surgery, all patients are instructed in and begin a standardised home-based postoperative rehabilitation protocol. Instruction is provided by physiotherapists at the orthopaedic clinic, with follow-up conducted by a primary care physiotherapist. All patients are scheduled for a 6-week post-surgery assessment by a physiotherapist at the orthopaedic clinic. Following this assessment, patients in both groups return to their primary care physiotherapist and continue rehabilitation based on their individual goals for as long as necessary. No further follow-up assessments are scheduled at the orthopaedic clinic.

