### Data collection and blinding

A questionnaire covering patient demographics, lifestyle behaviours, expectations and PROMs is mailed to patients, completed and brought to the baseline assessment, where objective function measures are conducted. At the baseline assessment, a triaxial accelerometer (activPAL) is attached to the front of the thigh of the affected leg and worn 24 hours a day for 7 days. The accelerometer is then returned to the trial coordinator using a pre-paid reply envelope.

Follow-up assessments are conducted immediately after the 8-week intervention and at 6, 12 and 52 weeks post-surgery. Waiting times for surgery will vary between patients, and if more than 4 weeks elapse between the post-intervention follow-up and surgery, an additional follow-up assessment will be scheduled approximately 1 week before surgery.

PROMs are collected at every follow-up assessment. Measures of objective function are conducted at the 8-week follow-up, 1 week before surgery and 6 weeks after surgery. The activPAL accelerometer is worn 24 hours a day for 7 days immediately after the 8-week follow-up and at the 12-week and 52-week postoperative follow-up assessments.

Outcome data are collected locally at each participating centre. All PROMs in the trial are administered via paper surveys. Measures of objective function are assessed by a physiotherapist blinded to group allocation. Physiotherapists performing these assessments are trained on two occasions before participating in the trial, during which pilot measurements of objective outcome measures are conducted under the supervision of the trial coordinator. The assessors also participate in monthly meetings with the trial coordinator throughout the trial to address potential issues.

Patients are not blinded to group allocation but are not informed of the trial hypothesis until data collection is complete. An overview of the trial timeline and data collection is provided in figure 1 and table 3.

**Table 3 T3:** Data collection/outcome measures

Data collection time points	Baseline	8-week follow-up	1-week preop follow-up (if necessary)	6-week postop follow-up	12-week postop follow-up	52-week postop follow-up
Demographics, lifestyle behaviours, expectations, etc	X					
PROMs						
FJS-12	X	X	X	X	X	**X**
Satisfaction						X
Mod-PEI-2	X	X	X	**X**	X	X
KOOS	X	X	X	X	X	X
IPAQ-sf	X	X	X	X	X	X
EQ5D-3L	X	X	X	X	X	X
Objective function						
Isometric quadriceps strength	X	X	X	**X**		
Active knee ROM	X	X	X	**X**		

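### The only injury category the protocol names can occur in the prehabilitation arm alone, so a like-for-like record of preoperative injuries in the two arms is not assured

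*Protocol article*

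**What the plan says.** The Adverse events section is one sentence: "Adverse events, including injuries sustained during intervention participation, re-surgeries (with reasons), postoperative infections and deaths, are recorded for all patients".

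The Randomisation section describes the arms as "the intervention group, comprising prehabilitation in addition to standard care (SC+P), or the control group, consisting of standard care only (SC"). Under Standard care, the preoperative content for controls is self-care plus one education session, and "No specific preoperative exercise advice is given".

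On recording before surgery, the Adherence section says of the physiotherapist's exercise journal in SC+P: "The journal tracks the number of exercises performed, variation of exercises, dosage and load used and the SANE score for each patient at every session". For controls, "any participation in ongoing exercise interventions outside the trial is recorded using patient-reported forms at baseline and at the 8-week and 1-week pre-surgery follow-ups". Those forms cover the type, duration and weekly frequency of exercise. Attendance at the education session is documented as well.

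Under Prehabilitation, SC+P patients who continue unsupervised after week 8 "have check-ins scheduled by phone or video conference every other week". Under Data collection and blinding, "PROMs are collected at every follow-up assessment". The follow-ups after baseline and before surgery are the 8-week one and a second about a week before surgery, held only if more than 4 weeks separate the post-intervention follow-up from surgery.

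**The concern.** The arms are treated differently only between randomisation and surgery. In that window the listed events are deaths and injuries linked to the intervention; re-surgeries and postoperative infections come later. A control patient who falls at home, or is hurt in exercise arranged outside the trial, has no event in a named category. An SC+P patient hurt in a session does. An SC+P patient who falls at home while not exercising also falls outside the named injury item, so a reduction in falls from strength and balance training would go unseen as well.

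The stake is the safety record. The strengthening exercises aim for a perceived exertion of 17–18, and patients may be up to 85 years old. The article hopes to influence guidelines. If a results table sets the named injury counts of the two arms next to each other, the control column is zero whatever happened to those patients.

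**Working it through.** The article states no harm rate and no harm comparison, so there is no figure of its own to reproduce. The check sets the sections side by side.

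**Step 1: in which arm can each named event occur before surgery?**

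| Named event | SC+P, before surgery | SC, before surgery |
|---|---|---|
| Injury while taking part in the intervention | possible | not possible (Randomisation; Standard care) |
| Re-surgery | postoperative | postoperative |
| Postoperative infection | postoperative | postoperative |
| Death | possible | possible |

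The only named non-fatal preoperative event belongs to one arm.

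**Step 2: how often could an event come to staff attention before surgery?**

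- SC+P: 2 sessions per week × 8 weeks = 16 scheduled sessions. Each has a knee-health rating beforehand and an entry in the staff journal. Those who go on unsupervised also have contact every second week.
- SC: the 8-week follow-up, plus the 1-week preoperative follow-up where held, so 1 or 2 scheduled trial contacts after baseline.
- Both arms have those 1 or 2 follow-ups and the education session, which is run by staff outside the trial. The difference is therefore at least the 16 sessions.

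**Step 3: does the article describe anything that evens this out?** The preoperative forms described specifically for controls concern outside exercise. The questionnaires and function tests at the 8-week and 1-week follow-ups are the same in both arms, but they measure the state of the knee and general health on the day. They do not count injuries or falls. The article describes no shared injury question.

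**Step 4: scale, under an assumption.** With 110 patients allocated 1:1 there are 110 / 2 = 55 per arm. Suppose 5% to 10% of controls had an injury needing care while waiting. This range is assumed and has no source in the article. Then 55 × 0.05 = 2.75 and 55 × 0.10 = 5.5, so about 3 to 6 events would lie outside the named categories. That is not a count of lost events, because an open list could still pick them up.

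**Step 5: effect on the main results.** The target of 110 is built from the Forgotten Joint Score-12 and the modified Patient Enablement Instrument-2 alone. Nothing in the adverse-event wording enters it or the primary comparison.

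**The case against.** The strongest reply is that the sentence is inclusive. It lists examples after the word *including*, gives no separate definition of preoperative harm, and excludes nothing. A reader might infer that preoperative harm is defined by the session-injury item, or that the sentence contradicts itself. Neither follows: recording can cover everyone even when one listed example arises in one arm only.

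A reader might also infer that the trial cannot compare harms before surgery at all. The article does not support that. Deaths are recorded in both arms. Knee worsening can be compared through the Knee injury and Osteoarthritis Outcome Score, EQ-5D-3L, Forgotten Joint Score-12 and function tests taken on the same schedule, the function tests by blinded assessors.

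Nor does the article show that the harm of prehabilitation will be overstated. Neither the aim nor the Analysis plan contains a between-arm harms comparison, and describing injuries caused by a programme is ordinary safety reporting. The control-arm exercise form belongs to adherence, so its content says little about how adverse events are collected. A fuller protocol may hold the event form and definitions, and their absence from an article is no fault.

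All of this stands, and it limits the point. What remains is that the article does more than leave detail out: it states an injury item and words it so that only one arm can meet it. An open list does not repair this by itself. Events that no one asks about are more likely to surface where staff meet the patient twice a week.

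**Conclusion.** The point holds in a limited form. The one named injury category is a structural zero in the standard-care arm, and preoperative staff contact is much heavier in SC+P (16 sessions in addition to the 1 or 2 follow-ups common to both arms). The text therefore does not assure a like-for-like record of preoperative injuries. This is an ascertainment weakness in the safety record, of modest weight. It leaves the sample size, the primary outcomes and their analysis unchanged.

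The conclusion rests on two readings: that intervention means the prehabilitation programme, as the Randomisation section implies, and that no common injury question exists elsewhere. If the full protocol already asks both arms the same question, only the wording of the article needs correcting. The number of events concerned cannot be derived from the article.

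**What to change.** In the Adverse events section, name injuries, including falls, between randomisation and surgery as an event recorded in both arms. Ask about them with one identical question on the existing paper forms at the 8-week follow-up and, where held, the 1-week preoperative follow-up. Base any between-arm presentation of preoperative harms on that item. Report injuries during intervention sessions separately, as a description of the SC+P programme.

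The cost is one question on forms already in use and a short protocol amendment. Recruitment is expected to run throughout 2026, so later patients can still be covered. Patients already past these visits will lack the item, so the amendment date and the number of patients asked in each arm should be reported. Where no 1-week follow-up is held, up to 4 weeks before surgery fall after the last preoperative form. That gap follows the same rule in both arms, and the period the question actually covers should be stated with the results.

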### Data management and patient confidentiality

All digital trial data are stored on a secure server managed by Region Östergötland. All physical trial documentation (envelopes, surveys, exercise protocols, etc) is stored in a fireproof locker accessible only to the research group. Patients are assigned a unique three-digit ID, and the key code is accessible only to the trial coordinator. Only coded data are shared among the authors in the research group.

### Sample size

To detect a difference in the MIC of 17.7 points (effect size 0.61) and the MCID of 13.7 points between the SC+P and SC groups in the FJS-12^16^ from baseline to the 52-week follow-up, and assuming a 0.6 proportion of total scores >21 points for the Mod-PEI-2 in the SC+P group versus 0.3 in the SC group at the 6-week follow-up, a total of 110 patients is targeted for inclusion across the two groups (80% power, 5% α-level, with an estimated 20% dropout included).

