### Analysis plan

All analyses will be performed using IBM SPSS Statistics software, V.29, applying intention-to-treat and per-protocol approaches with an α-level of 0.05. Demographic data will be presented as mean or median with SD or IQR for quantitative variables, and as frequencies and percentages for categorical variables.

Depending on measurement scale and distribution, differences between groups at baseline and for primary and secondary outcomes at each follow-up assessment will be analysed using independent samples t-tests or non-parametric equivalent tests. Longitudinal changes within groups from baseline to follow-up time points will be analysed using linear mixed models or generalised linear models, with baseline measurements included as covariates. Multiple linear regression and logistic regression will be used to analyse predictor variables for the primary outcomes (FJS-12 and Mod-PEI-2). Furthermore, analyses of primary and secondary outcomes will be adjusted, if necessary, for differences in intervention delivery and adherence, duration of participation, surgical procedures and postoperative physiotherapy care.

Multiple analyses will be performed using α-level adjustment methods, such as the Bonferroni method. In the intention-to-treat analysis, a sensitivity analysis will be performed to quantify the magnitude of missing data from patients lost to follow-up. Appropriate statistical methods will be used to account for missing data in the analysis, depending on the characteristics of the missing data. If there is extensive missing data, a second table of baseline characteristics will be presented only for patients included in the final analysis. The proportion of missing outcomes per group, characteristics of patients with missing data and possible reasons for missing outcome data will be presented.

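### 110 patients do not give the stated 80% power for the 13.7-point MCID on the FJS-12; on the protocol's own figures the power is about 59%

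*Protocol article*

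**What the plan says.** The Sample size section of the protocol article is a single sentence with one total. For the FJS-12 it reads "To detect a difference in the MIC of 17.7 points (effect size 0.61) and the MCID of 13.7 points", with both differences placed between the two randomised groups and the time frame given as "from baseline to the 52-week follow-up". The effect size stands next to the 17.7 points. The 13.7 points have no effect size of their own, and no SD for the FJS-12 is printed anywhere in the article.

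The same sentence adds the enablement outcome: "assuming a 0.6 proportion of total scores >21 points for the Mod-PEI-2 in the SC+P group versus 0.3 in the SC group". It concludes that "a total of 110 patients is targeted for inclusion across the two groups", with "80% power, 5% α-level, with an estimated 20% dropout included".

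The Analysis plan section names the independent samples t-test, or a non-parametric equivalent, for comparing the groups at each follow-up. It sets the significance level with "applying intention-to-treat and per-protocol approaches with an α-level of 0.05". The Randomisation section gives 1:1 allocation.

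**The concern.** The two FJS-12 targets are joined by a plain conjunction and share one sample size and one power figure, so the sentence promises 80% power for each. For the same outcome, groups and sample size, a difference that is 4 points smaller must have less power. If 110 is just enough for 17.7 points, it falls short for 13.7.

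The shortfall affects the more important of the two values. The FJS-12 at 52 weeks is a primary outcome, and 13.7 points is what the protocol labels the minimal clinically important difference. A reader who trusts the paragraph could take a non-significant FJS-12 result as good evidence against a benefit of that size. At 59% power, a true 13.7-point benefit would be missed about 4 times in 10.

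**Working it through.** **Inputs, from the Sample size section unless noted**
- Differences: 17.7 points with effect size 0.61, and 13.7 points with none.
- Power 80%, alpha 5%, dropout 20%, total 110.
- 1:1 allocation (Randomisation) and t-test (Analysis plan).
- Sidedness is not stated. Two-sided is assumed because it reproduces 110.

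**Step 1: implied SD.** 17.7 / 0.61 = 29.0.

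**Step 2: reproduce 110.** The normal approximation is n per arm = 2(1.960 + 0.842)² / d². With d = 0.61 this is 15.70 / 0.372 = 42.2, so 43 per arm, and 86 / 0.8 = 107.5, so 108. The exact t-test calculation gives 43.2, so 44 per arm, and 88 / 0.8 = 110, which is the stated total. A one-sided test gives 34 per arm and 85 in total, which does not match. The Mod-PEI-2 proportions of 0.6 and 0.3 need 42 per arm, or 105 in total (123 with continuity correction), so they do not produce 110 either.

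**Step 3: effect size for the MCID.** 13.7 / 29.0 = 0.472.

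**Step 4: power at the planned size.** 110 × 0.8 = 88 analysed, 44 per arm. Approximate power is Φ(d√(n/2) − 1.960), with √(44/2) = 4.690:
- 17.7 points: Φ(0.61 × 4.690 − 1.960) = Φ(0.90) = 81.6%
- 13.7 points: Φ(0.472 × 4.690 − 1.960) = Φ(0.25) = 60.0%

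| Difference | Effect size | Power, 44 per arm (t-test) | Power, 55 per arm, no dropout (t-test) | Needed for 80% power |
|---|---|---|---|---|
| 17.7 | 0.61 | 80.8% | 88.7% | 44 per arm, 110 recruited |
| 13.7 | 0.472 | 59.1% | 68.9% | 72 per arm, 144 analysed, 144/0.8 = 180 recruited |

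**Step 5: detectable difference.** With 44 per arm, 80% power corresponds to an effect size of 0.604, and 0.604 × 29.0 ≈ 17.5 points.

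**Step 6: sensitivity of the 59% (t-test, 44 per arm)**
- Rounding of 0.61 (0.605 to 0.615): 58.4% to 59.8%.
- One-sided 5% test: 71%.
- Other SDs, as assumptions: 65% at 27, 72% at 25, 81% at 22.5. The SD that gives 80% is 13.7 / 0.604 ≈ 22.7.
- Alpha 0.025, if a Bonferroni split over the two primary outcomes were applied: about 48% for 13.7 points and 72% for 17.7.

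**The case against.** The arithmetic is not in dispute. The strongest objection is that the protocol prints no SD, so 59% depends on carrying the SD implied by one pair of figures over to the other difference. The two values are different quantities, a minimal important change and a minimal clinically important difference. The sentence does not say whether both sit on the change score or on the 52-week score. Moreover, an effect size of 0.61 gives 110 whichever difference it belongs to: if it had been meant for 13.7, the SD would be 13.7 / 0.61 = 22.5 and that target would have its 80%. It is fair that the figure is conditional on the SD, and it should be reported that way. But the text attaches 0.61 to 17.7 and offers no second SD. If 0.61 did belong to 13.7, the sentence would be wrong in a different place, because power for 17.7 would then be about 95%.

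A second objection is baseline adjustment. If 29.0 is the SD of the 52-week score and baseline is a covariate, power for 13.7 points rises to about 63% at an assumed baseline correlation of 0.3 and 72% at 0.5. It reaches 80% at about 0.62. The protocol states no correlation. The Analysis plan names a t-test for comparing the groups and mentions baseline covariates for the models of change within groups, so this does not support the claim as written. The planned multiplicity adjustment would push power the other way.

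Finally, it can be said that nobody has announced an intention to misread a null result, and that a wording correction is minor. No passage announces such a misreading, but the paragraph as written invites it.

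**Conclusion.** The concern holds. With 88 analysed patients, the design has about 81% power for 17.7 points and about 59% for 13.7, so the 80% claim is right for the first and wrong for the second. This rests on an SD of 29.0 for both differences, a two-sided 5% t-test and the full 20% dropout. No dropout, a one-sided test or rounding of the effect size does not bring 13.7 points to 80%. Only an SD of about 22.7 or less, or a baseline correlation above 0.6 used in an adjusted between-group analysis, would do so, and the protocol states neither. Because this is a power statement for a primary outcome at the protocol's own threshold of importance, it must be corrected.

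**What to change.** Rewrite the FJS-12 part of the Sample size section along these lines: 110 recruited patients (88 analysed after 20% dropout) give about 81% power to detect a 17.7-point difference, assuming an SD of 29.0 and a two-sided t-test at 0.05; for the MCID of 13.7 points the power is about 59%. Delete the claim of 80% power for 13.7. If the sponsor holds a separate SD and calculation for the MCID, print those instead and reconcile them with the pairing of 17.7 and 0.61. If the primary FJS-12 test will use an adjusted alpha, quote power at that alpha.

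Add a sentence on interpretation: the FJS-12 difference will be judged from its 95% confidence interval against 13.7 points, and a non-significant result will not be described as showing no important effect unless the interval excludes 13.7.

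The cost is wording only, with one figure becoming less favourable. The correction itself needs no extra patients. The protocol expects recruitment throughout 2026 and data collection to the end of 2027, so on that timetable the text can be put right before results are known.
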